#### Control procedure (M-MIST)

This will be performed as described in the literature [14, 28]:Scaling and root planing using conventional ultrasonic tips and curettes under local anaesthesiaPeriodontal re-evaluation and charting 3 months laterIn case of residual PPD > 5 mm, surgical access with the following protocol:Ideally, the experimental sites will be accessed with the M-MIST technique (elevation of buccal flap only with simplified or modified papilla preservation incisions, no papilla elevation) and carefully debrided.When a defect wraps around the lingual aspect of a tooth and M-MIST is not applicable, elevation of the interdental soft tissues becomes necessary and MIST becomes the preferred approach. This consists of elevation of small buccal and lingual flaps (with modified papilla preservation incision in case of interproximal space width of at least 2 mm or otherwise simplified papilla preservation [29].When the position of the residual buccal/lingual bony wall(s) is very deep and difficult or impossible to reach with the above-described minimal incision of the defect-associated interdental space, the flap(s) will be further extended mesially or distally involving one extra interdental space to obtain a larger flap reflection [29].

Should the FMPS not reach the threshold below 25% before surgery, additional oral hygiene (OH) instructions will be given before proceeding with the surgical intervention. If after three additional OH sessions, the FMPS is still not below 25%, the patient will be exited from the study as not considered suitable for surgery [30]. Measurements will be taken during surgery to characterise the defect anatomy (number of walls, depth and width). No regenerative material/devices will be applied. Flaps will be sutured with modified internal mattress sutures (and single interrupted sutures if necessary).

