#### Need for further treatment during and following study completion

Treatment to sites other than the selected ‘intrabony site’ throughout the study will consist of subgingival debridement (as allocated by randomisation in test and control patients) and supportive therapy as per protocol. The need for other surgical interventions will be reviewed following the 15 months follow-up. Should deterioration be detected during the study in any sites, where urgent need for surgery or antibiotics is needed, this will be carried out in additional visits during the study and will be documented in the Case Report Forms (CRFs). Following the 15 months follow-up, the possible need for further treatment will be assessed based on residual PPDs > 5 mm [4, 31].

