The sample size calculation was based on the assumption that the proposed modified MINST protocol is an acceptable alternative to the M-MIST protocol (non-inferiority), with the advantage of reduced costs and morbidity. A non-inferiority margin of 1 mm is considered to be the largest difference that is acceptable between MINST and M-MIST (a lower threshold than the expected difference in bone gain between regenerative surgeries and open flap debridement in intrabony defects) [12] for MINST to be adopted in clinical practices because of the associated advantages of MINST. Single-flap approaches such as M-MIST have previously been reported to lead to radiographic bone gains from 1.8 ± 1.2 mm [37] to 2 mm [38] to 3.5 ± 1.0 mm [14] in small trials. MINST has been reported to lead to 2.4 ± 2.1 mm radiographic bone gain in a retrospective study [17]. Therefore, we assume that the two protocols lead to the same bone gain for the sample size calculation. Accounting for a 10% drop-out rate and using a pooled standard deviation of 1.27, recruiting *n* = 66 participants will be sufficient to confer 90% power to reject the inferiority null hypothesis. Should the true mean bone gain difference between MINST and M-MIST be 0.19 mm in favour of M-MINST, the study would retain a statistical power of 80%. The primary outcome analysis will compare the intrabony defect depth between treatment groups at 15 months using a general linear analysis of covariance (ANCOVA) model with treatment as a factor and the corresponding baseline value as a covariate and adjusting for pre-specified prognostic baseline factors (age, FMPS, BMI, defect angle, tooth mobility). For the primary efficacy endpoint, non-inferiority of M-MIST to MINST could be claimed if the lower limit of the 95% confidence interval (for the difference in mean change of radiographic intrabony defect depth change) is greater than − 1.0 mm. The primary outcome analysis will be the per-protocol analysis; the intention-to-treat analysis will be considered as the sensitivity analysis. For other non-inferiority endpoints the per-protocol analysis will also be considered the main analysis. The superiority endpoint will be analysed on an intention-to-treat basis. Subject-based and site-based analyses will be conducted. The PROM analysis will be based on linear or logistic regression (for continuous/categorical variables) comparing PROM scores or categories of scores at follow-up (3, 9 and 15 months post-intervention) between the two groups, accounting for the respective scores at baseline. We will also look at the minimally important difference for PROMs where applicable, such as in the case of the OIDP, and whether any difference between the two groups is clinically meaningful.

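### Non-inferiority can be claimed on the per-protocol analysis even if intention-to-treat misses the margin, although per-protocol membership may depend on response or arm

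*Protocol article*

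**What the plan says.** All references are to the protocol article.

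- **Analysis hierarchy (Statistical analysis plan).** "The primary outcome analysis will be the per-protocol analysis; the intention-to-treat analysis will be considered as the sensitivity analysis". The same choice extends to the rest of the non-inferiority family: "For other non-inferiority endpoints the per-protocol analysis will also be considered the main analysis".
- **Decision rule (same section).** The claim depends on one criterion, a lower 95% confidence limit above -1.0 mm. The margin is explained as follows: "A non-inferiority margin of 1 mm is considered to be the largest difference that is acceptable between MINST and M-MIST". Nothing makes the claim conditional on the intention-to-treat result.
- **Rescue (Need for further treatment during and following study completion).** The trigger is "Should deterioration be detected during the study in any sites, where urgent need for surgery or antibiotics is needed". The treatment is given within the study and recorded in the case report forms. The rule is not limited to one arm.
- **Plaque-score exit (Control procedure).** If the full-mouth plaque score is still not below 25% after three extra hygiene sessions, "the patient will be exited from the study as not considered suitable for surgery". The rule appears only in the control arm.
- **Conditional surgery (Control procedure).** Controls are operated on only if a residual pocket deeper than 5 mm is found at the 3-month re-evaluation.
- **Sample size (Statistical analysis plan).** "Accounting for a 10% drop-out rate and using a pooled standard deviation of 1.27", 66 participants are said to give 90% power.

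**The concern.** Making the per-protocol analysis primary is a familiar choice in non-inferiority trials, because intention-to-treat can blur a real difference. That protection holds only if exclusion from the per-protocol set is unrelated to outcome. Here three written rules create events after randomisation that are tied to response or to arm, and each is a plausible reason for leaving the set. A set chosen partly by how patients healed no longer has the protection of randomisation, and the nominal 2.5% error of the claim is not assured.

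Intention-to-treat would be the natural check, but as written it cannot stop the claim. It is also imperfect by itself. A radiograph taken after rescue surgery counts as healing under the allocated treatment, and a patient exited from the study may have no 15-month radiograph. Neither analysis is sufficient alone, which is the reason for requiring both. The Discussion says a non-inferior result might support MINST as an alternative to surgery, so the rule behind the claim matters.

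**Working it through.** **Inputs from the protocol article.** Margin 1.0 mm, SD 1.27 mm, true difference 0 for planning, 66 patients, 1:1 allocation between treatments, 10% drop-out. That leaves 33 × 0.9 = 29.7 analysed per arm. Differences are MINST minus M-MIST in bone gain.

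**1. Reproducing the plan's figure.** n per arm = 2 × SD² × (z₁₋α + z₀.₉₀)² / margin².
- One-sided 0.05: 2 × 1.6129 × (1.645 + 1.282)² = 27.6, so 28, or 29 with the t distribution. 29 / 0.9 = 32.2, so 33 per arm, 66 in total. The plan's number reproduces.
- One-sided 0.025, which a two-sided 95% interval implies: 34 per arm, 68 in total, 76 after drop-out. This does not match 66.

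**2. Effect of a selection shift on the false-claim rate.** Standard error = 1.27 × √(2/29.7) = 0.330 mm. If the true deficit equals the margin and selection shifts the estimate by b, the false-claim rate is the probability that a noncentral t (noncentrality b/SE) exceeds its one-sided 2.5% critical value.

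| Shift b (towards MINST is positive) | b/SE | False-claim rate |
|---|---|---|
| -0.20 mm | -0.61 | 0.5% |
| 0 | 0 | 2.5% |
| +0.20 mm | 0.61 | 8.6% (8.1% with 29.7 vs 24 patients) |

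A shift of 0.20 mm would arise, for example, if 20% of controls were dropped and these had healed 1.0 mm better than the rest: 0.20 × 1.0 = 0.20 mm. Both inputs are assumptions.

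A shift of -0.20 mm costs power instead. At a true difference of 0, normal approximation, power falls from Φ(1.0/0.330 - 1.96) = 0.86 to Φ(0.8/0.330 - 1.96) = 0.68.

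**3. Which event pushes which way.** Simulation with 30 per arm, true difference -1.0 mm, and an assumed correlation of 0.3 to 0.8 between the exclusion trigger and 15-month gain. With no exclusions the simulated error was 2.3%.

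| Exclusion (assumed share) | Shift | False-claim rate |
|---|---|---|
| Worst 10% of MINST (rescued) | +0.07 to +0.19 mm | 3.7% to 8.1% |
| Worst 10% of both arms (rescue in both) | about 0 | about 2.3% |
| Worst 10% of controls (as the plaque exit may do) | -0.08 to -0.20 mm | 1.4% to 0.5% |
| Best 20% of controls (only if surgery were required for the set) | +0.13 to +0.35 mm | 5.4% to 17.4% |

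The sign depends on which exclusions are applied and in which arm.

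**4. Cost of requiring both analyses.** Simulation with true difference 0, 95% intervals, 30 per arm in intention-to-treat and 26 per arm in per-protocol, exclusions unrelated to outcome. Power is about 79% for per-protocol alone and about 78% for both.

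**The case against.** The strongest reply is that a per-protocol primary analysis with an intention-to-treat sensitivity analysis is an accepted design, that the definition of the per-protocol set may properly sit in an analysis plan not shown here, and that no rates of rescue or exit are known. All of this stands. The missing definition is not the point; the point is the stated hierarchy, which lets the claim go through without agreement.

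Four stronger readings are tempting, and the documents do not support them.

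- *Controls left unoperated are protocol departures.* A reader might infer this, but a control whose pocket closes and who has no surgery has followed the written control procedure. Bias arises only if the set were to require surgery, which the article does not say.
- *Rescue is arm-specific.* The rule is driven by outcome but open to both arms. If it removed equal shares of poor responders from each, the shift would be about zero.
- *The bias is known to favour MINST.* The one rule written for a single arm is the plaque-score exit in controls. If it removes poorer healers, it works against MINST, so the net direction is unsettled.
- *Per-protocol exclusions cut power from 90% to 80%.* With 20% total loss the t-based power at one-sided 0.025 is indeed about 80%, but it is already about 85% at the planned 10% loss. Half of the gap is therefore the mismatch between one-sided 0.05 and the 95% interval, a separate matter. In the normal approximation, going from 10% to 20% loss costs 0.859 - 0.816 = 4 points at 0.025 and 0.918 - 0.888 = 3 points at 0.05.

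**Conclusion.** The concern holds in a limited form. The article fixes a rule under which non-inferiority can be claimed from the per-protocol set while intention-to-treat misses the 1 mm margin, and it contains events after randomisation, linked to response or arm, that could determine membership of that set. The resulting bias may go either way. A shift of 0.20 mm, one fifth of the margin, would move the 2.5% false-claim rate to about 8% if it favoured MINST, or to about 0.5% with a loss of power if it favoured M-MIST. These sizes rest on assumed exclusion shares, an assumed healing difference and the plan's SD of 1.27 mm. They show how sensitive the rule is and do not predict what will happen in this trial. The correction should be made: it changes a stated rule, costs little, and does not depend on knowing the direction of bias.

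**What to change.** 1. **Decision rule.** Claim non-inferiority only if the lower 95% confidence limit exceeds -1.0 mm in both the per-protocol and the intention-to-treat analyses. Apply the same rule to the other non-inferiority endpoints, each with its own margin.
2. **Unoperated controls.** State that controls not operated on under the protocol's own pocket-depth rule belong to the per-protocol control group.
3. **Plaque-score exits.** Follow these patients to the 15-month radiograph, subject to their consent, and include them in intention-to-treat.
4. **Rescued study sites.** In both arms, report a sensitivity analysis that does not credit post-rescue healing to the allocated treatment. Standardised radiographs are taken only at baseline, 9 and 15 months, so simply carrying the baseline depth forward would assign zero healing to anyone rescued before 9 months and should not be the default. Setting post-rescue values to missing and imputing them over a stated range of assumptions is one option.

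**Cost.** Protocol and analysis-plan wording, follow-up of a few exited patients, and a small loss of power because both analyses must succeed: about one to two percentage points in the check above (79% to 78%). That check assumed exclusions unrelated to outcome. No change to treatment or recruitment is needed.

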
#### Data management

All data will be entered in a dedicated secure database application with a secure web connection (REDCap). A customised REDCap project will be set up and will be used to cover all data capture for the study. Different levels of access will be set up for the different end users/study team delegates. Data will be proofed for entry errors before being locked and exported for analysis.

#### Randomisation and allocation concealment

Following the baseline visit, all participants enrolled in the study will be randomly assigned to one of the two treatment groups and whether or not to be included into the GTI substudy; that is, individual-level randomisation to MINST, M-MIST, MINST + GTI or M-MIST + GTI will be performed using a 2:2:1:1 allocation ratio. Random permuted block randomisation with block sizes 6 and 12 will be employed. The centralised online randomisation service ‘Sealed Envelope’ with web front-end will be used ensuring allocation concealment. No minimisation or stratification is planned.

#### Blinding

Due to the nature of the intervention, only blinding of all outcome examiners is possible. Both participants and clinicians administering treatment will be unblinded. Members of the Trial Steering Committee and other study team members will remain blinded to treatment allocation until the randomisation code is broken (after the last follow-up data are recorded and the database locked).

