### Study visits

Each subject will attend between 8 and 13 study visits over a period of approximately 16 months (see Table 1 for the study visit schedule and procedures). All the visits will take place in the clinics of Barts and The London Dental Hospital. The schedule of assessments is also presented in Fig. 1 (flowchart of study plan and visits) and in Fig. 2 in the form of a Consolidated Standards of Reporting Trials (CONSORT) diagram.

**Table 1 Tab1:** Schedule of study visits and procedures

Protocol procedures	Visit 1	Visit 2	Visit 2a	Visit 2b	Visit 3	Visit 4	Visit 4a	Visit 4b	Visit 4c	Visit 5	Visit 6	Visit 7	Visit 8
	Baseline	Side I treatment	1day post-treatment	5 days post-treatment	Side II treatment	3 months post- treatment	Surgical treatment	1 week suture removal	1 month review	6 months post- treatment	9 months post- treatment	12 months post- treatment	15 months post- treatment
	Week 0		GTI subgroup only	GTI subgroup only			Only subjects in MIST group	Only subjects in MIST group	Only subjects in MIST group				
Verification inclusion/exclusion, informed consent	x												
Medical/dental history & updates Demographics	x	x	x	x	x	x	x	x	x	x	x	x	x
Height, weight, waist circumference	x												
3D facial imaging	x		x	x		x		x	x		x		
Periodontal measurements (PPD, gingival recession, bleeding on probing, mobility and furcation involvement)	x					x				x	x		x
Plaque assessment	x					x				x	x	x	x
PROMs	x		x	x		x		x			x		x
Early healing index	x							x					
Standardised X-ray		x									x		x
GCF collection	x		x	x		x					x		x
Subgingival plaque collection/saliva	x		x	x		x					x		x
Debridement	x					x				x		x	
Impression for radiographic stent	x												
Dentine/root sensitivity measurements	x		x	x		x					x		x

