#### Clinical periodontal assessment

The following periodontal measurements will be taken by the calibrated examiner (author VK) at six sites/tooth using a manual University of North Carolina (UNC-15) periodontal probe (Hu-Friedy, Chicago, IL, USA): dichotomous full-mouth plaque score (FMPS) [19], full-mouth PPD, recession of the gingival margin from the cemento-enamel junction (CEJ), dichotomous 6-point full-mouth bleeding score (FMBS) on probing [19], tooth mobility [20] and furcation involvement with a Nabers probe (Hu-Friedy) [21]. Clinical attachment level (CAL) will be calculated as PPD+ recession. The early healing index [22] will be measured for controls 1 week after surgery. Dentine/root sensitivity (DS/RS) will be assessed on the tested intrabony tooth and on the two neighboring teeth, following isolation using cotton wool rolls, by using an evaporative/thermal stimulus from a 1-s blast of air from a dental unit syringe at 40–65 psi (19–23 °C) directed perpendicular to the tooth surface at a distance of 0.5–1 cm to the exposed root surface (evaporative examination) [23]. Following the air blast, the subject will be given a visual analogue scale (VAS) form to complete each assessment. The VAS is scored from 0 = no pain to 10 = extreme pain, and the subject can indicate the degree of discomfort by indicating either a numerical value from 0 to 10 or by marking vertically across the VAS.

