#### Repeatability

Following initial training, for a repeatability exercise the examiner and back-up examiner will perform repeated examinations on 10 subjects for PPD and recession with at least 15 min separation. Upon completion of all measurements, intra-examiner repeatability for PPD measurements will be assessed. In order to test inter-examiner repeatability, at least 10 subjects will be probed twice (once by each examiner). The reproducibility of the examiner will be tested using the Bland–Altman approach [24] and by calculating Lin’s concordance correlation coefficient [25]. A coefficient of repeatability less than ±2 mm in 95% of the cases is considered acceptable. If this target is not achieved, further examiner assessment and training will be carried out before a new reproducibility exercise is performed.

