#### Radiographic analyses

Standardised radiographs of selected study sites will be taken at baseline and at the 9 and 15 months follow-up visits using the parallel technique with a customised holder and an occlusal platform, which will allow a cold-cure acrylic resin occlusal registration to be made (bite index), facilitating relocation of the holder and preserving the projection geometry in subsequent radiographs. Aluminium step wedges will be used as a densitometric reference in an attempt to minimise errors due to variation in exposure time and/or film processing which may result in false positive analysis [26]. The linear radiographic measurement analysis will be carried out by a single calibrated examiner using semi-automated radiographic software with specific landmarks, as described by Nibali et al. [27]. In brief, horizontal and vertical bone loss of the intrabony defects will be measured after identifying the following landmarks in periapical radiographs: CEJ on the tooth with the intrabony defect, most coronal part of the alveolar bone and most apical part of the alveolar bone crest, where the periodontal ligament space was judged to retain its normal width. The radiographs will be analysed by the same trained and calibrated examiner in a masked, random order with the use of a computer software measurement tool (Emago®, Oral Diagnostic Systems, Amsterdam, the Netherlands).

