#### Test procedure (MINST)

Based on our previous study [17], a modified MINST protocol for this study consists of the following:Local anaesthesia by infiltration without adrenaline in the study site (not intrasulcular anaesthesia)Thorough debridement of the root surface up to the bottom of the periodontal pocket under local anaesthesiaAttempt to minimise the trauma to the soft tissues and especially to the papilla, using a subpapillary access for debridement (trying not to touch the most coronal part of the interdental papilla)Use of exclusively piezo-electric devices with specific thin and delicate tipsDeliberately avoid ‘smoothing’ the root surface or performing gingival curettageUse of 3–4× magnification loupesAttempt to stimulate the formation of a stable blood clot, by natural filling of the intrabony defect with blood following debridement (no use of any subgingival rinses).

This modified protocol differs slightly from the published protocol [17] in the use of a subpapillary access; exclusively piezo-electric devices (no curettes); the specific use of anaesthesia without adrenaline and no intrasulcular anaesthesia; and the first subgingival probing at 6 months post-treatment (rather than at 3 months). These slight refinements from the earlier studies [17] aim to further reduce tissue trauma and to stimulate a stable blood clot for optimal healing. This modified MINST protocol will be applied to the intrabony sites and all other affected sites in test patients. The same treatment protocol is currently being tested in a separate single-arm prospective multicentre study (ClinicalTrials.gov reference NCT03741374).

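### Table 1 and the test procedure disagree on 3-month probing; if the test procedure is followed and the PPD/CAL examiner does that visit, the arm can be inferred before the later readings

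*Protocol article*

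**What the plan says.** All places are in the protocol article.

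- **Blinding.** "only blinding of all outcome examiners is possible". Participants and treating clinicians are declared unblinded.
- **Clinical periodontal assessment.** "The following periodontal measurements will be taken by the calibrated examiner", in the singular, for PPD, recession, bleeding, plaque, mobility and furcation. CAL is the sum of PPD and recession. No visit is excepted. The same section says that the early healing index "will be measured for controls 1 week after surgery" and does not say who scores it.
- **Test procedure (MINST).** One of the listed differences from the earlier published protocol is "the first subgingival probing at 6 months post-treatment (rather than at 3 months"). The modified protocol is applied to the intrabony sites and all other affected sites.
- **Control procedure (M-MIST).** Controls are re-evaluated and charted 3 months after initial therapy, and residual PPD above 5 mm leads to surgery. No assessor is named.
- **Study visits, Table 1.** The row "Periodontal measurements (PPD, gingival recession, bleeding on probing, mobility and furcation involvement") is marked at Visits 1, 4, 5, 6 and 8, that is, at baseline and at 3, 6, 9 and 15 months. Visits 4a to 4c carry the label "Only subjects in MIST group"; Visit 4 carries no arm label.
- **Repeatability.** A second, trained rater exists: "the examiner and back-up examiner will perform repeated examinations on 10 subjects".
- **Radiographic analyses.** "The radiographs will be analysed by the same trained and calibrated examiner in a masked, random order".

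**The concern.** The trial is described as examiner-blind, and for manual probing nothing else is masked. If one arm is probed at 3 months and the other is deliberately left unprobed, whoever does that visit can tell the arms apart from the task itself. If the same person later measures PPD and recession, those readings are no longer blind.

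PPD and CAL change are the first secondary outcomes in the Statistical analysis plan section, and the Discussion ties a non-inferiority conclusion to clinical as well as radiographic defect reductions. Probing depth depends on the observer, so knowledge of the arm could move the between-arm difference. There is also a trap in the repair: a correction that only brings Table 1 into line with the test procedure would settle the schedule and, with nothing said about the assessor, leave the examiner exposed.

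**Working it through.** The plan gives no figure on this point, so the check is a comparison of passages.

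**Step 1: what happens at 3 months (Visit 4).**
- Under the test and control procedures, controls are charted and modified MINST patients are not probed until 6 months.
- Under Table 1, PPD and recession are measured at Visit 4 with no arm restriction. The table does restrict by arm elsewhere (Visits 4a to 4c), so the missing label cannot be put down to a format that has no way of showing arms.
- The two readings cannot both be followed for a test patient.

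**Step 2: who does it.** The Clinical periodontal assessment section gives these measurements to one designated examiner without excepting any visit. The control procedure names nobody. The Repeatability section mentions a back-up examiner, but only in the calibration exercise. By default, then, the designated examiner does Visit 4. This is the natural reading, not an explicit statement.

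**Step 3: combine the two.**

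| 3-month schedule followed | Designated examiner does or attends Visit 4 | Another person does Visit 4, records withheld |
|---|---|---|
| Test procedure (controls only charted) | Arm can be inferred before the 6-, 9- and 15-month readings | Examiner stays blind |
| Table 1 (both arms charted) | No inference from Visit 4, but the stated delay in the test procedure is breached | Examiner stays blind; the same breach |

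Only the upper left cell unblinds through Visit 4. It needs both conditions. Where both hold, the route does not depend on surgery being done: a control without residual deep pockets is still charted.

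**Step 4: a second route.** The early healing index is taken only in controls, 1 week after surgery (Visit 4b in Table 1). If the designated examiner scores it, the arm of operated controls is known whichever schedule is used. The assessor is not stated.

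**Step 5: which outcomes are exposed.** PPD and recession, and through them CAL, are measured at three visits after Visit 4 (6, 9 and 15 months). The primary outcome is not exposed, because the radiographs are read masked and in random order.

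**The case against.** The strongest reply is that the premise is unsettled. The trial's only visit schedule charts both arms at 3 months, and on that schedule the Visit 4 route does not exist. Even if the test procedure prevails, a chart that decides on surgery could naturally be taken by the treating clinician, who is already unblinded, or by the back-up examiner. An assignment consistent with the Blinding section is therefore available. The article also condenses a fuller protocol, and rostering may be set out there.

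Much of this stands, and it rules out several stronger readings that a reader might infer:

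- *That unblinding is certain, or shown for every patient.* It is not: it needs both conditions in the table, and the document fixes neither.
- *That a single examiner does all the probing.* The description as a single calibrated examiner belongs to the radiographic reader. For probing there is one designated examiner with a back-up.
- *That the error rate of a non-inferiority claim on PPD or CAL can be quantified.* The 1.27 mm standard deviation and the 1 mm margin belong to the radiographic outcome. The document gives neither for PPD or CAL, and nothing in it supports a particular reading shift or its direction.

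What does not stand is the argument that this is only missing detail. The article states the arm definitions, the assessor and the visits, and two of its statements on 3-month probing contradict each other. One way of resolving them, read with the stated assessor, conflicts with the stated blinding. A back-up examiner could solve this, but the article does not say that this person will be used at Visit 4.

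**Conclusion.** The firm finding is a contradiction: the Test procedure section and Table 1 disagree on whether modified MINST patients are probed at 3 months, and they must be reconciled. This review takes no view on which schedule is right.

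The blinding point is conditional on that. If the test procedure is followed, and if the designated examiner does or attends the 3-month visit, that examiner can infer the arm before the 6-, 9- and 15-month PPD and recession readings, contrary to the Blinding section. The first condition is one of two schedules in the document; the second is the default reading of the Clinical periodontal assessment section.

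The reach is limited to PPD, CAL and other chairside measurements by the same person. A reader might infer that the non-inferiority result itself is compromised; the masked, randomly ordered radiographic reading does not support that. No numerical size can be given for any bias in PPD or CAL. The point is worth acting on because the remedy is cheap and protects the first-listed secondary outcomes whichever way the schedule is settled.

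**What to change.** When the Test procedure section and Table 1 are reconciled, add to both the Clinical periodontal assessment and Blinding sections that:

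1. the blinded examiner for PPD and CAL does not attend Visit 4 or any control-only assessment, including the early healing index 1 week after surgery;
2. that examiner has no access to the records of those visits; and
3. those assessments are done by the back-up examiner trained in the repeatability exercise, or by the unblinded treating clinician.

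The blinded examiner then measures at Visits 1, 5, 6 and 8.

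**Cost.** Wording and re-rostering, with no new staff, no new visit and no change in treatment. There are two downsides. The 3-month PPD comes from a different examiner from the later readings; the planned inter-examiner exercise gives some information on agreement if the back-up examiner is used, but does not cover a treating clinician. And a back-up examiner used in this way can no longer stand in as a blinded assessor for those patients, so cover for absence at the later visits has to be arranged with that in mind.
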